### Outcomes

The primary outcome measure is the percentage of intervention group participants who achieved at least 5% weight gain compared to the control group.

The secondary outcome measures include mean between-group differences of the following variables from baseline to the end of the 12th week:

I.Anthropometric measurementsBody weightHeightBody mass index (BMI)Mid-upper arm circumference (MUAC)Calf circumference (CC)Waist circumferenceTriceps skin fold thicknessII.Body compositionDXA lean body mass and fat massIII.Biochemical parametersFull Blood Count (FBC)Hs-CRP (C-reactive protein)Serum albuminTotal cholesterolSerum total 25-hydroxy vitamin DIV.Functional capacityHand grip strengthKnee extensionActivities of daily living — Barthel indexV.FrailtyFive fried model indicatorsVI.Respiratory muscle strength (peak expiratory flow rate)VII.Energy and macronutrient intake per dayVIII.Cognitive status (Montreal Cognitive Assessment)IX.Physical activity levelPhysical Activity Scale for the Elderly (PASE)International Physical Activity Questionnaire (IPAQ – short form)

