### Sample size

The sample size calculation was based on studies indicating that a weight gain of 5% can be expected with an ONS intervention, and is sufficient to achieve an overall improvement in nutritional status [23]. A clinically relevant difference was defined as an increase in this fraction to 75% or greater in the treatment arm. Hence, a total of 50 adults will be recruited for the study (alpha, 5%; beta, 10%; drop-out rate, 20%) after the screening for eligibility against inclusion/exclusion criteria. Then, participants will be randomly assigned into two groups (*n*=25 intervention and *n*=25 control). The formula used for sample size calculation was as follows:$${n}_{B} =\left( \frac{{p}_{A \left( 1- {p}_{A}\right)}}{k} \right)+{\left(\frac{z1- \frac{\propto }{2 } + z1- \beta }{{p}_{A-{P}_{B}}}\right)}^{2}$$$${n}_{B}$$ = Sample size in one arm

*P*_*A*_ = Proportion of participants expected to achieve 5% improvement in body weight in the control group (0.3) [23]

*P*_*B*_ = Proportion of participants expected to achieve 5% improvement in body weight in the intervention group (0.75) [23]

*Κ* = Sampling ratio (1:1)

*Z*_*α*_ = Critical value of the normal distribution at *α* (*α* is 0.05 and the critical value is 1.96)

*Z*_*β*_ =Critical value of the normal distribution at *β* (*β* is 0.1)

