### Methods in analysis to handle protocol non-adherence and any statistical methods to handle missing data

Each participant’s consumption of the ONS will be monitored on a weekly basis to assess adherence to the intervention. If a participant is unable to consume the supplement continuously for more than five days due to hospitalization or any other reason, they will be considered as “non-adherent” to the intervention. Using Multiple imputation methods accessible in SPSS, the primary outcome data of the participants will be randomized to the intervention but non-adherent participants will be imputed [29].

We expect the proportion of missing data to be below 5% for the primary outcome. We will not perform multiple imputations for the primary outcome unless more than 5% of the data are missing. The secondary outcomes will be assessed in a full analysis set.

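### The imputation rule for the primary outcome is triggered by non-adherence in the ONS arm alone, not by a missing weight, and conflicts with the 5% rule that follows it

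*Protocol article*

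**What the plan says.** The primary outcome is binary and compares the arms (*Outcomes*): "The primary outcome measure is the percentage of intervention group participants who achieved at least 5% weight gain compared to the control group".

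The section *Methods in analysis to handle protocol non-adherence and any statistical methods to handle missing data* then makes five statements.

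- Non-adherence is defined by intake alone. It applies to a participant who is "unable to consume the supplement continuously for more than five days due to hospitalization or any other reason".
- For these participants, "the primary outcome data of the participants will be randomized to the intervention but non-adherent participants will be imputed".
- On the amount of missing data: "We expect the proportion of missing data to be below 5% for the primary outcome".
- On when to impute: "We will not perform multiple imputations for the primary outcome unless more than 5% of the data are missing".
- On the analysis set: "The secondary outcomes will be assessed in a full analysis set". No set is named for the primary outcome.

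Elsewhere, *Sample size* allows for 20% drop-out. Table 2 schedules body weight at baseline, week 4 and week 12 in both arms. *Strategies to improve adherence to intervention* defines percentage compliance over 84 days.

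**The concern.** Non-adherence and missing data are different things. Participants live in the care home where weight is measured, so a resident who misses six days of supplement in hospital can still be weighed at week 12. Nothing in the imputation sentence limits it to residents who were not weighed.

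The rule is also one-sided. Controls receive water, and nothing equivalent is written for them. A control who falls ill and loses weight keeps that result. An ONS participant with the same illness may have the result replaced by a model value. Because illness affects both intake and weight, the replaced outcomes are likely to be poorer than average.

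What is at stake is the question that the primary analysis answers. With observed data it is whether offering ONS raises the proportion who gain at least 5%. With the literal rule it moves towards what would have happened had everyone in one arm adhered, set against controls as observed.

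The two paragraphs also give the analyst no single instruction, in a trial with 25 participants per arm.

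**Working it through.** **1. The plan's own figure.** Inputs from *Sample size*: control 0.30, intervention 0.75, two-sided alpha 0.05 (1.96), beta 0.10 (1.282), drop-out 20%. The usual unpooled formula gives

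n = [0.30×0.70 + 0.75×0.25] × [(1.96 + 1.282)/0.45]² = 0.3975 × 51.9 = 20.6 per arm.

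Then 20.6 × 1.2 = 24.8, so 25 per arm and 50 in total, as stated. Sample size is not in dispute here. The calculation shows that the 20% drop-out allowance is built into N.

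**2. The trigger against actual intake.** Missing 6 consecutive days leaves 78 of 84 doses, or 92.9% compliance, and counts as non-adherent. Taking every second dose gives 42 of 84, or 50%, with no run longer than one day, and does not count. Neither pattern implies a missing weight.

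**3. The two paragraphs side by side.** 5% of 50 is 2.5, so the threshold is passed at 3 participants.

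- If non-adherent participants count as missing, three of them open the gate and the first rule operates.
- If they do not count and everyone is weighed, the gate stays shut and the preceding sentence has no effect.

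The text does not say which applies. The planned drop-out would be 20% × 50 = 10 participants. If those weights were missing, the gate would be open.

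**4. The same weight in two analyses.** Mean body weight is a secondary outcome (*Outcomes*) and is to be analysed in a full analysis set. One week-12 weight could therefore be used as measured there and replaced in the primary analysis.

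**5. Size of the effect if the literal rule is applied.** The following are assumptions that the documents do not give: q, the non-adherent share of the ONS arm; pn, the response rate of non-adherers; and 0.75 as the response rate of adherers (the protocol gives 0.75 for the whole intervention arm). Control is 0.30.

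- Difference on measured data: (1−q)×0.75 + q×pn − 0.30.
- Difference if non-adherers are imputed from ONS adherers: 0.75 − 0.30 = 0.45.
- Excess: q × (0.75 − pn).

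| q | pn | Measured | Imputed | Excess |
|---|---|---|---|---|
| 0.1 | 0.5 | 0.425 | 0.45 | 0.025 |
| 0.2 | 0.3 | 0.36 | 0.45 | 0.09 |
| 0.3 | 0.1 | 0.255 | 0.45 | 0.195 |
| 0.2 | 0.75 | 0.45 | 0.45 | 0 |
| 0.2 | 0.9 | 0.48 | 0.45 | −0.03 |

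**6. No true effect.** Let both arms respond at 0.30 overall. ONS adherers then respond at (0.30 − q×pn)/(1−q). With q = 0.2 and pn = 0.1 this is 0.28/0.8 = 0.35, a false difference of +0.05. With q = 0.2 and pn = 0.4 it is 0.22/0.8 = 0.275, a difference of −0.025.

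**7. Imputation pooled over both arms.** With q = 0.2 the donors are 25 controls at 0.30 and 20 adherers at 0.75, so the mean is (7.5 + 15)/45 = 0.50. The imputed ONS rate is 0.8×0.75 + 0.2×0.50 = 0.70, a difference of 0.40. On measured data the difference is 0.36 if pn = 0.30 and 0.45 if pn = 0.75, so the error can go either way.

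**The case against.** A reader might infer that the protocol commits to overwriting measured weights and so fixes a result biased towards ONS. The documents do not support that, for three reasons.

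- Replacement of measured weights is never stated. It is the natural reading of an unconditional but ungrammatical sentence, under a heading that covers both non-adherence and missing data. The two paragraphs could together mean that outcomes missing among non-adherent participants are imputed. Some will be missing, because *Criteria for discontinuing or modifying allocated intervention* has participants with related adverse events leave the study.
- If the 5% gate governs and nearly everyone is weighed, no imputation takes place and the excess in step 5 does not arise.
- The direction depends on an imputation model that is not given and on how non-adherers fare. Steps 5 to 7 show that the excess can vanish or reverse.

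It is also fair to say that the article never uses the term intention-to-treat, so the departure is from a standard and not from a stated commitment. A 20% sample-size margin and an expectation of under 5% missing do not strictly contradict each other. The alternate-day pattern is hypothetical, given daily calls and nurse-supported dosing. The choice of imputation variables and sensitivity analyses belongs in an SAP, and their absence here is no finding.

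These points limit the claim about bias. They do not repair the text: the trigger is still adherence, the rule still names one arm, and its relation to the 5% gate is still undefined.

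**Conclusion.** The point holds as a defect of wording that governs the primary analysis. As written, non-adherence and not a missing weight triggers imputation, in the ONS arm only, and the next paragraph sets a condition that conflicts with this rule or silently limits it. The expectation of under 5% missing also sits awkwardly with the 20% drop-out. This needs to be resolved before analysis.

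Bias towards ONS is probable, not demonstrated. It requires that the literal rule is applied, that values are imputed within the arm, and that non-adherers respond less than adherers. On those assumptions, with 20% non-adherent and 30% response among them, the difference is overstated by 9 points (45 against 36). For 10% to 30% non-adherent with 10% to 50% response, the overstatement is 2.5 to 19.5 points. None of these non-adherence or response rates for non-adherers comes from the documents.

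**What to change.** Rewrite the section so that it states the following:

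1. Every measured week-12 weight enters the primary analysis in the arm to which the participant was randomised, whatever the adherence.
2. Imputation applies only to week-12 weights that are actually missing, by the same rule in both arms.
3. Adherence is handled only in a supplementary analysis, using the percentage compliance already defined in *Strategies to improve adherence to intervention*.
4. The 5% rule counts missing weights only, or is dropped, and the expected amount of missing data is reconciled with the 20% drop-out in *Sample size*.

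The cost is an amendment to the wording. The weights are already scheduled, and N does not change. The downside for the sponsor is that the estimate may become less favourable to ONS.

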The study faces several challenges including the high number of tests and the potential increased risk of dropouts. Therefore, participants will be carefully informed about the various tests before and throughout the study to reduce the possibility of dropouts. Further challenges may occur in recruiting participants and their subsequent compliance with supplementation. In order to limit the impact of these challenges, recruitment will be performed by health care personnel, physiotherapists, and nutritionists and caregivers will be thoroughly instructed about the preparation methods of the ONS and advised to monitor carefully the participants’ consumption of the ONS. Additional challenges may occur in transporting participants to the Nawaloka Hospitals Colombo (about 10–20 km away from the elderly care institution) for DXA scanning and blood investigations. Because of the frailty of many participants, special care will be needed during this time.

Finally, a major limitation of the trial may be contamination bias when participants in the control group inadvertently receive the ONS. Participants will be educated as much as possible against contamination and clear information about the purposes of the trial will be provided with supplements provided to caregivers in person. The absence of blinding may also introduce performance bias; however, blinding either participants or investigators is not possible due to the nature of the intervention.

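### The 20% drop-out allowance and the below-5% missing-data expectation are not reconciled, and two imputation rules for the primary outcome conflict when 5% or less is missing

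*Protocol article*

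**What the plan says.** Three places in the protocol article bear on loss of the primary outcome, which is the proportion gaining at least 5% of body weight by week 12.

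- **Sample size.** The total of 50 (25 per arm) is given with "alpha, 5%; beta, 10%; drop-out rate, 20"%.
- **Methods in analysis to handle protocol non-adherence and missing data.** The second paragraph states "We expect the proportion of missing data to be below 5% for the primary outcome", rules out multiple imputation of that outcome unless the missing share exceeds 5%, and adds "The secondary outcomes will be assessed in a full analysis set". The first paragraph defines non-adherence as more than five continuous days without the supplement. It then says, in a garbled sentence, that primary-outcome data of non-adherent participants randomised to the intervention will be multiply imputed. No threshold is attached.
- **Discussion.** It acknowledges that "The study faces several challenges including the high number of tests and the potential increased risk of dropouts".

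The section on discontinuing the intervention also has participants with a study-related adverse event leave the study.

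**The concern.** The sample size and the missing-data section use very different figures for loss, and the choice of primary analysis turns on which proves right. The 20% allowance is there to make up for participants without a usable primary outcome. The text gives no reason why fewer than 5% of those outcomes should be missing.

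The missing-data section also gives two instructions for the same outcome. One imputes because of non-adherence, in the supplement arm only and at any level of missingness. The other imputes because data are missing, and only above 5%. An analyst with one or two missing weights could follow either. As worded, the non-adherence rule also reaches participants who were weighed at week 12. Replacing their measured weights in one arm only would treat the arms differently and discard observed outcomes.

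**Working it through.** **1. Is the 20% a working input to N = 50?**

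Inputs from the Sample size section: "Proportion of participants expected to achieve 5% improvement in body weight in the control group (0.3"), "Proportion of participants expected to achieve 5% improvement in body weight in the intervention group (0.75"), α = 0.05 two-sided ("is 0.05 and the critical value is 1.96"), β = 0.10 (z = 1.2816), 1:1 allocation.

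Unpooled two-proportion formula:

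n = [p_A(1−p_A) + p_B(1−p_B)] × (1.96 + 1.2816)² / (p_A − p_B)²

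= (0.21 + 0.1875) × 10.508 / 0.2025 = 20.63 per arm.

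- 20.63 × 1.2 = 24.75, so 25 per arm and 50 in total. This reproduces the plan.
- Dividing instead, 20.63 / 0.8 = 25.78, so 26 per arm and 52 in total.
- With a 5% allowance, 21 / 0.95 = 22.1, so 23 per arm and 46 in total.

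The formula as printed, with a plus sign between its two terms, gives about 52 per arm. It is taken here as a misprint of the unpooled formula. The step from 21 to 25 per arm comes from the 20% allowance.

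**2. The two figures on one scale**

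- 20% of 50 = 10 participants.
- 5% of 50 = 2.5, so below 5% means at most 2, and imputation starts at 3 missing.

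**3. How often the 5% trigger would fire**

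X is the number missing of 50, taken as binomial with loss rate d. P(X ≥ 3) = 1 − P(X ≤ 2).

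| Loss rate d | P(X ≤ 2) | P(X ≥ 3): imputation used |
|---|---|---|
| 20% | 0.001 | 0.999 |
| 10% | 0.112 | 0.888 |
| 5% | 0.541 | 0.459 |

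**4. The two imputation rules side by side**

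| Participant | Non-adherence rule | 5% rule, at most 2 missing | 5% rule, 3 or more missing |
|---|---|---|---|
| Supplement arm, non-adherent, weight missing | impute | do not impute | impute |
| Supplement arm, non-adherent, weight measured | impute, as worded | nothing missing | nothing missing |
| Supplement arm, adherent, weight missing | silent | do not impute | impute |
| Control arm, weight missing | silent | do not impute | impute |

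For missing weights the rules clash only in the first row, and only when at most 2 of 50 are missing; above 5% both call for imputation. The second row is a separate problem and arises at any level of missingness. Each participant in an arm of 25 carries 1/25 = 4 percentage points of that arm's responder rate.

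**The case against.** The strongest defence is that an allowance and an expectation are different things. A cautious sponsor may size for 20% and expect less. Participants live in a care home, weight is measured on site, and staff are phoned before each visit, so stopping the supplement need not mean a missing weight. The Discussion speaks only of a potential increase in drop-outs. The trigger also acts on missingness actually observed: if 20% are lost, imputation is carried out. All of this stands. It does not explain the gap between the two figures, and it leaves the conflict between the two imputation rules untouched.

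Three stronger readings are tempting, and the document does not support them.

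- *The two figures cannot both hold.* A reader might infer this by equating drop-out with a missing week-12 weight and the allowance with a forecast. The text does neither, so the figures are unreconciled, not strictly contradictory.
- *Mean weight change will rest only on participants who were measured, while the responder rate rests on everyone.* Imputation is mentioned only for the primary outcome, but a full analysis set does not mean completers only. Its definition may properly sit in a statistical analysis plan that is not shown.
- *The trigger puts up to 40 points of uncertainty on the result.* With 5 lost per arm and 15/20 versus 6/20 responding, the extreme bounds on the difference run from 16 points (15/25 − 11/25) to 56 points (20/25 − 6/25). That is the case of 10 missing, where the plan does impute. Where the 5% rule withholds imputation, at most 2 are missing and the same bounds span about 8 points (2/25, or 1/25 in each arm).

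**Conclusion.** The point holds as an unexplained inconsistency together with a conflict between two stated rules. The plan's own figures put loss at 10 of 50 in one place and at most 2 of 50 in another. If loss is 20%, multiple imputation becomes the primary analysis with probability 0.999. If it is 5%, the choice of method is close to even (0.459). These probabilities assume independent losses at a common rate and that a drop-out has no week-12 weight.

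The rule conflict rests on the natural reading of a garbled sentence: that non-adherent participants in the supplement arm have their primary outcome imputed. On that reading the rules disagree when 5% or less is missing, and measured weights in one arm could be replaced at any level of missingness. How many participants this would affect cannot be computed, because the protocol gives no expected rate of non-adherence. The change is worth making before analysis, since both percentages and both rules are printed in the protocol and are not details left to a later document.

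**What to change.** - **Reconcile the loss figures.** Bring the missing-data expectation into line with the 20% allowance, or say why far fewer primary outcomes should be missing than the allowance implies.
- **Use one rule.** Replace both the 5% on/off trigger and the one-arm non-adherence rule with a single rule for both arms. Measured week-12 weights are kept regardless of adherence. Only missing ones are multiply imputed, from arm, baseline weight, week-4 weight (already in the schedule of assessments) and sex.
- **Use one weight.** Derive 5% responder status, and preferably mean weight change, from that same observed or imputed weight.
- **Add one sensitivity analysis.** Count every participant without a week-12 weight as not having gained 5%. In the example above this gives 15/25 versus 6/25, a difference of 36 points.

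The cost is a rewording of the missing-data section, slightly more analysis work, and a less favourable stated expectation for missing data if it is aligned with the allowance. No new measurements are needed.

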### Plans to give access to the full protocol, participant-level data, and statistical code

Full protocol, participant data, and statistical code will be available from the principal investigator upon reasonable request after the publication of the study results.

## Oversight and monitoring

### Composition of the coordinating center and trial steering committee

The coordinating center is located at the Health and Wellness Unit, Faculty of Medicine University of Colombo. The coordinating center consists of research assistants and data collectors. They are responsible for manual operations, facilitation of study recruitment, data collection ensuring the protocol is implemented as planned, reviewing the study progress on a regular basis, and upholding good clinical practice at all times. The primary decision-making body of the study will be the trial steering committee, consisting of the principal investigator and the co-investigators. The steering committee will be responsible for all aspects of the finalization of the study protocol, logistics, and organization of the trial. The information on other committees and groups providing day-to-day support for the trial is summarized in Table 3.

**Table 3 Tab3:** Committee and supporting groups involved in the trial

**Committee/supporting group**	**Consistency**	**Involvement**
**Recourse persons**	Specialist in sports and exercise medicine	Training the data collectors who will be responsible for obtaining muscle strength parameters, specifically knee extension and hand grip strength.
	Consultant physician in geriatrics	Provide training on various questionnaires used in the study such as the Barthel index, MoCA, IPAQ, PASE, and GAIT assessment.
	Specialist in Nutrition	Provide training on obtaining all anthropometric measurements, screening the participants using MNA-SF, and obtaining 24-h dietary recalls.
**Management of the elders’ home**	President Manager Treasurer	Make necessary arrangements and facilitate the data collection process. This involves coordinating logistics, ensuring a conducive environment for data collection, and managing any administrative tasks related to the trial.
	Matron	Involved in handling the participants with care during the data collection process
**Team of care givers**	Six nurses working in the elderly care home	Actively contribute to the trial by facilitating the supplementation process before bedtime. Nurses will ensure that the participants receive the necessary ONS as per the protocol. Additionally, the team of caregivers is involved in taking video calls for remote monitoring and collection of containers to assess compliance with the intervention. Their involvement strengthens the adherence and compliance of the participants throughout the trial period.

*MoCA* Montreal Cognitive Assessment, *IPAQ* International Physical Activity Questionnaire, *PASE* Physical Activity Scale for the Elderly, *MNA-SF* Mini Nutrition Assessment Short Form, *ONS* oral nutritional supplement

